## Abstract

**Background:**

The prevalence of diabetes has been growing rapidly in developing countries. This causes devastating economic burdens and increases demands on the health care system. Therefore, there is an urgent need to find a cost-effective and multi-faceted approach for diabetes care. Peer support models provide a potentially low-cost, flexible means which complements the current existing health care services. In this way, trained peer leaders can become qualified extensions to a formal healthcare system, capable of assisting education delivery and bolstering the efforts of professional staff. As such, creating a cultural specific peer support program and determining whether it is acceptable and cost-effective in rural communities of China is crucial. This study aims to implement and evaluate biophysical and psychosocial outcomes of peer support program for people with type 2 diabetes in rural communities, and to explore the program’s feasibility and sustainability in China.

**Methods/Design:**

This study is a cluster randomised controlled trial. All consenting patients will be randomised by community staff members to receive either peer support or the control care. The data collection and analysis including social demographics, health status, psychosocial status, economic status and biomedical measures will be collected at baseline, 6 months, and 12 months. The primary indicator measured is the change in HbA1c, whereas secondary indicators include biophysical, psychosocial functioning and other lifestyle factors. Finally, economic evaluations will determine whether the program is cost effective.

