### Study design and setting

This study is a cluster randomised controlled trial implemented and reported in accordance with the requirements of the CONSORT statement [13] and its extension to cluster randomised trials [14]. The participants were randomly designated to either an intervention arm, which implements the usual care system and the peer support intervention, or a control arm which implements a usual care system, with geographical location being the unit of cluster randomisation.

All participants are patients with type 2 diabetes who receive primary health care at 12 rural community health centres located in Liu-he District, Nanjing, and Gao-gou Town, Huaian, in Jiang Su province. The study team coordinates and works hand-in-hand with the staff members at each community health centres to implement and monitor the study.

Figure 1 is a CONSORT diagram of the study design.

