#### Group allocation

Community health centres will be stratified by size and existing structure of primary diabetes care service. Allocation to intervention or control group is governed by a random number generation process using SAS 9.1 statistical software independently.

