### Sample size calculation

Sample size and power calculations are performed for the main outcome of interest-difference in mean HbA1c levels-using effect sizes and standard deviations derived from multiple published trials of patient-education interventions. Using a non-inferiority design based on clinically relevant difference of HbA1c of 0.5%, standard deviation of 1.5, and groups of 8–15 participants per randomisation group for 80% power at two-sided 5% significance, 150 participants are required to complete the study procedures. Allowing for a 20% drop-out from randomisation to completion of the trial, it is anticipated that we would require 180 subjects in each arm to be randomised in the study.

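### The randomised unit is given variously as the patient, the health centre and a group of 8–15; these cannot be one unit, and the stated power holds only for patients

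*Protocol article*

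**What the plan says.** The protocol article describes the allocation in four places.

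- **Abstract, Methods/Design:** "This study is a cluster randomised controlled trial", followed by "All consenting patients will be randomised by community staff members to receive either peer support or the control care".
- **Study design and setting:** the participants are said to have been randomly designated to an arm, "with geographical location being the unit of cluster randomisation". The next paragraph places the patients in "12 rural community health centres located in Liu-he District, Nanjing, and Gao-gou Town, Huaian, in Jiang Su province".
- **Group allocation:** "Community health centres will be stratified by size and existing structure of primary diabetes care service". Then: "Allocation to intervention or control group is governed by a random number generation process using SAS 9.1 statistical software independently".
- **Sample size calculation:** the calculation is based on "groups of 8–15 participants per randomisation group", an HbA1c difference of 0.5%, a standard deviation of 1.5, 80% power and a two-sided 5% level. It arrives at 150 completers and 180 randomised in each arm.

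Two other sections bear on this. Under Intervention group, 8–15 is the size of the sets of patients formed by area of residence and given a peer leader. Under Data analysis, clustering by clinic site and by primary care provider is to be examined, with adjustment only where it seems necessary.

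**The concern.** The article makes incompatible positive statements about what was randomised, so this is more than detail left to a fuller document. The unit decides which variation the arm difference is tested against, how many degrees of freedom the test has, and what cluster size belongs in the sample size. If centres were randomised but the trial is sized and analysed as though patients were, the standard error is too small whenever patients in a centre resemble one another. The stated power is then not achieved.

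The Abstract also has community staff doing the randomising, while Group allocation has an independent software process. The article does not say how the two fit together, which leaves it unclear who controlled the assignment.

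**Working it through.** **1. Can the stated units be the same thing?**
- 180 per arm × 2 arms = 360 randomised. 360 / 12 centres = 30 per centre. With 150 completers per arm, 300 / 12 = 25 completers per centre.
- A group of 8–15 is therefore not a centre; a centre of 30 would hold about 2 (30/15) to 4 (30/8 = 3.75) such groups.
- The groups of 8–15 are described only for the intervention arm, as peer-leader groups. Sets formed in one arm cannot be what was allocated between two arms.
- A single patient is neither a centre nor a group. Geographical location can be read as the area a centre serves, in which case it agrees with Group allocation.

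Three incompatible units remain: patient, centre and group of 8–15.

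**2. The plan's own figure**

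For individually randomised patients, n per arm = 2 × (1.96 + 0.84)² × SD² / difference² = 2 × 7.85 × 1.5² / 0.5² = 141.3, so 142. A non-inferiority margin of 0.5% at one-sided 2.5% also gives 142. The plan states 150, read here as per arm because the next sentence gives 180 per arm. This is slightly more than 142, and power at 150 per arm is 82.3%.

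The margin over the patient-level figure is 150 / 141.3 = 1.06. Treated as a design effect 1 + (m − 1) × ICC, it covers an ICC of only 0.062/7 = 0.009 for m = 8 or 0.062/14 = 0.004 for m = 15. For a centre of 25 it covers 0.062/24 = 0.003. The figure contains almost no allowance for clustering.

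**3. Degrees of freedom for the arm comparison**
- Patients: 300 − 2 = 298.
- Centres: 12 − 2 = 10, before any are spent on the strata.

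**4. Power at 150 completers per arm, centres as the unit**

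Assumptions: 6 centres per arm, 25 completers each, equal sizes. The article gives no ICC, so a range is shown. Design effect DE = 1 + 24 × ICC; standard error = 1.5 × √(2 × DE / 150); power from the noncentral t distribution with 10 degrees of freedom and noncentrality 0.5 / standard error.

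| Assumed ICC | DE | Power |
|---|---|---|
| 0 | 1.00 | 74% |
| 0.01 | 1.24 | 65% |
| 0.02 | 1.48 | 57% |
| 0.05 | 2.20 | 42% |
| 0.10 | 3.40 | 29% |

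The 74% at ICC 0, against 82% for patients, comes from the small number of centres alone.

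**5. Effect of using 8–15 as the cluster size**

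At an assumed ICC of 0.05, DE is 1 + 7 × 0.05 = 1.35 for m = 8 and 1 + 14 × 0.05 = 1.70 for m = 15, against 2.20 for a centre of 25. Entering the peer-group size when centres were randomised understates the inflation needed.

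**The case against.** The strongest reply is that the article calls itself a cluster trial consistently, so the Abstract sentence about patients is loose wording. Geographical location most naturally means a centre's catchment. The 8–15 phrase may describe peer groups lying within an arm and not a randomised unit at all. On that reading only the Abstract, and the phrase about participants being designated, disagree with Group allocation. Much of this stands: location need not count as a separate unit. But the sample size section still attaches 8–15 to randomisation and gives no cluster size for the centre, and its result is close to the patient-level figure. The conflict therefore reaches the numbers as well as the wording.

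Three stronger inferences are not supported.

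- A reader might infer that the two named areas are the randomised units, one per arm, leaving no degrees of freedom. Stratifying centres by size and care structure would make no sense with two units, so Group allocation rules this out.
- A reader might infer two contradictory allocators. The software may have generated the sequence and the staff may only have applied it; both statements could be true. The article does not say so, and clarification is all that can be asked.
- A reader might infer that staff who recruit patients also allocate them. Under Participants, clinicians and staff recommend peer leader candidates, primary care clinicians exclude patients, and the study team contacts the eligible ones. Nothing shows that those who select patients also assign them.

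An article may also leave the timing of allocation release to the full protocol, so its absence is not an error.

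**Conclusion.** The concern holds: the article does not fix one unit of randomisation, and patient, centre and group of 8–15 are mutually incompatible. The consequence is material. The test has about 298 degrees of freedom if patients were randomised, and at most 10 if the 12 centres were. Power with 150 completers per arm is about 82% in the first case. In the second it is about 74% at ICC 0 and about 65% to 29% at assumed ICCs of 0.01 to 0.10. The contradiction and the degrees of freedom follow from the article's own statements and counts. The centre-level power figures rest on assumed ICCs, 6 equal centres per arm, and reading 150 as per arm; unequal centres or degrees of freedom spent on strata would lower them further. On allocation, the documents support a request to reconcile two sentences and do not show that concealment failed.

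**What to change.** - **Unit.** Name the community health centre as the randomised unit throughout, since Group allocation is the most specific description. Correct the Abstract, Study design and setting, and Sample size calculation to match.
- **Sample size.** Replace 8–15 with the number of participants per centre (about 30 randomised, 25 completing) as the cluster size. State an ICC with its basis, and restate the power for 12 centres. Keep 8–15 only as the peer-group size.
- **Analysis.** Make the primary analysis under Data analysis account for centre as the randomised unit in every case, not conditionally on evidence of clustering.
- **Allocation.** In the Abstract, replace randomisation by community staff with the independent software allocation of Group allocation. If staff only carried that allocation out, say so.
- **Recruitment.** If a centre's allocation was known before its patients were identified, report this and compare recruitment and exclusions by arm.

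The cost is mostly wording, plus one revised power calculation. The drawback is that the stated power becomes less favourable.

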**Discussion:**

This protocol is a cluster randomized, controlled trial of group-based peer support for people with type 2 diabetes in the community settings of rural China. Results from this trial may provide evidence to the effectiveness of peer support; furthermore, they will provide valuable information concerning the acceptability and feasibility of a new approach to improve diabetes self-management among resource-constrained settings.

**Trial registration:**

ClinicalTrials.gov Identifier: NCT02119572, April 18, 2014.

## Background

Diabetes is a growing health problem worldwide. It is estimated that 382 million people live with diabetes around the world, and by 2035, that number will surge to 592 million [1]. Diabetes mellitus imposes a huge economic burden on national health care systems globally. The global health expenditures for diabetes in 2030 is forecasted to increase 30% to 34% from 2010. Developing countries will experience a twenty-year growth rate of 67% while the developed countries will have a rate of 27% [2]. A systematic review showed that diabetes affects 6.8%, or one out of every 15 people living in rural areas worldwide. From 1990–2010, the prevalence in low-middle income countries grew fourfold, while in high-income countries, the prevalence was twofold higher [3]. Furthermore, rural populations often live in worse socioeconomic conditions and have poor literacy skills compared with their urban counterparts [4]. As such, there is an urgent need to find innovative and effective solutions to help citizens in rural communities especially in low-middle income countries to successfully manage diabetes [5].

China has the largest number of individuals with diabetes mellitus; 113.9 million (11.6%) adults at age 18 or older have diabetes and 493.4 million adults (50.1%) are pre-diabetic. The prevalence of diabetes and pre-diabetes in rural areas is an estimated 10.3% and 50.9% respectively [6]. Considering the problem of a growing diabetic population, health professional shortages, and an under-financed health care system in China, a effective strategy is crucial. Providing education programs to a fast growing number of people with diabetes, particularly the poor and less-educated rural community, presents a huge challenge to Chinese health care system. To improve diabetes care and positively influence health outcomes, new approaches need to be developed that are both effective and feasible in Chinese rural communities [7].

Nowadays, peer support models have been widely recognized as a promising solution. The concept of peer support emphasizes a patient-centered approach as “the provision of emotional, appraisal and informational assistance by a created social network member who possesses experiential knowledge of a specific behavior or stressor and similar characteristics as the target population, to address a health-related issue of a potentially or actually stressed focal person” [8]. Although the WHO reviewed the use of peer support programs for people with diabetes and found numerous patient benefits, such as glycemic control and increase in quality of life, further evaluations are needed before peer support interventions can be integrated into the existing policy for diabetes management [9]. A systematic review by Jeremy Dale and colleagues found that peer support programs exhibit a latent potential towards improving health outcomes in adults living with diabetes. However the evidence-based review also identified the evaluation’s inconsistency and limitations, emphasizing the need for additional data related to cost effectiveness in future research [10]. This study will seek to show that peer support models provide a potentially low-cost, flexible compliment to formal health care services [11].Trained peer leaders can become extensions, or adjuncts to a formal healthcare system, thereby assisting with education delivery and bolstering the efforts of health care professionals [7]. In the current Chinese health care system, diabetes education has not been incorporated, and rural populations with diabetes have not yet acknowledged the responsibility for their own disease or adopted recommended health behaviors. A survey using anonymous standardized patients showed that baseline-educated rural clinicians are not yet prepared to act as the front line fighters in China’s primary care system, or equipped to tackle problems in health education [12].Therefore, exploring effective strategies to support diabetes in rural communities is desperately needed.

This article is a study protocol for a cluster randomised controlled trial for a peer support programs in a rural community within China. Our aim is to implement and evaluate a peer support program for people with type 2 diabetes within a specified local rural community. This program is designed to allow the participants to meet and share their self-management challenges, to explore and develop strategies to overcome these challenges, as well as sustain health behavior change using the experience and support derived from the groups. This study will give valuable information about the effectiveness, acceptability and feasibility of a novel way to improve diabetes self-management among developing countries.

## Methods

### Objectives

This study aims to implement and evaluate the biophysical and psychosocial outcomes of a culturally specific peer support program using a cluster randomized controlled trial in patients with type 2 diabetes and to determine whether it is an acceptable, cost effective intervention in the rural community health care centers. The study’s objectives are as follows:To establish a culturally appropriate and feasible diabetes peer leader education curriculum by assessing participants’ adaptiveness to curriculum components, changes in trainees’ knowledge, attitudes, self-care skills and peer support outcomes.To establish a diabetes management network between the hospital, the community, and peer groups, and explore its feasibility and sustainability.To assess the following measures across peer support and control groups: HbA1c, AGE, blood lipids, blood glucose, blood pressure, BMI, medication adherence, knowledge, reported self-efficacy, self-care activities, quality of life, trait affect, life satisfaction, depression, anxiety, and stress.To evaluate differences in cost efficiency between the intervention group and the comparison group.

### Study design and setting

This study is a cluster randomised controlled trial implemented and reported in accordance with the requirements of the CONSORT statement [13] and its extension to cluster randomised trials [14]. The participants were randomly designated to either an intervention arm, which implements the usual care system and the peer support intervention, or a control arm which implements a usual care system, with geographical location being the unit of cluster randomisation.

All participants are patients with type 2 diabetes who receive primary health care at 12 rural community health centres located in Liu-he District, Nanjing, and Gao-gou Town, Huaian, in Jiang Su province. The study team coordinates and works hand-in-hand with the staff members at each community health centres to implement and monitor the study.

Figure 1 is a CONSORT diagram of the study design.

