### Data analysis

Social demographic data and health status of the study subjects are presented as frequencies (percentage) for categorical variables, and means ± standard deviations for continuous variables. Comparison of patients characteristics between groups will be checked by means of T-tests or χ^2^ tests, or non-parametric equivalents. Repeated measures analysis of variance and multilevel analysis for longitudinal data will be used to examine longitudinal differences between groups on primary and secondary outcome measures. Evaluation of intervention effectiveness will be by intention to treat using the above statistical tests. Evidence of clustering by clinic site and primary care provider will be examined and adjusted for analyses as needed. If significant differences in baseline characteristics are found, analyses will be repeated adjusting for these differences using ANOVA and logistic regression for multivariate analyses. Analysis of covariance (i.e. linear regression models for 12-month measurements with baseline scores and intervention arm as covariates) will estimate the changes from baseline to 12 months that can be attributed to the peer support intervention. Sensitivity analyses will be performed to estimate the effects of missing data using different assumptions (e.g. imputed values).The EuroQoL 5 dimensional health state measure (EQ5D) score at base-line and follow-up can be converted into utility weights using the EQ5D algorithm [34], which then allow for the calculation of quality adjusted life years(QALYs). Economic analyses will be employed to estimate direct and indirect cost analysis, the cost per QALY gained and incremental cost-effectiveness ratios. Sensitivity analysis will be undertaken to test the stability of the analysis in terms of the cost inputs and health outcomes. All analyses will be carried out with SPSS 10.0 software.

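### The 150 completers per arm come from an individual-level calculation; with 12 randomised centres a centre-level test on about 10 degrees of freedom has 74% power at best without baseline adjustment, and less with any clustering.

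*Protocol article*

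**What the plan says.** Under Study design and setting, the protocol article describes a cluster randomised trial in patients "who receive primary health care at 12 rural community health centres", "with geographical location being the unit of cluster randomisation". Group allocation says that the health centres are stratified by size and by how their diabetes care is organised, and then describes the random allocation.

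The Sample size calculation takes a "clinically relevant difference of HbA1c of 0.5%, standard deviation of 1.5" and concludes that "for 80% power at two-sided 5% significance, 150 participants are required to complete the study procedures". It then adds a dropout allowance and arrives at the statement that "we would require 180 subjects in each arm to be randomised in the study". It mentions groups of 8 to 15, but gives no ICC, design effect or number of clusters.

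On analysis, "Repeated measures analysis of variance and multilevel analysis for longitudinal data will be used to examine longitudinal differences between groups". Clustering by clinic site and provider is to be examined and adjusted for where needed. No reference distribution or degrees of freedom are given for the arm effect.

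**The concern.** When whole centres are randomised, the arm comparison is judged against variation between centres. Twelve centres give only 12 − 2 = 10 degrees of freedom for estimating that variation, however many patients each centre contributes. A power figure that treats 300 completers as independently randomised leaves out two things: the variance inflation from clustering, and the larger critical value that goes with few clusters. The second loss remains even when the ICC is zero, so adding a design effect alone would not repair the figure.

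At stake is whether the trial has the power it claims for HbA1c. There is also a risk in the analysis: a model that includes centre but treats the between-centre variance as known can give an interval that is too narrow.

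**Working it through.** **Inputs from the document.** Difference 0.5, SD 1.5, two-sided 5%, 80% power, 150 completers, 20% dropout, 180 randomised per arm (Sample size calculation); 12 centres (Study design and setting). The 150 is per arm, because 150 × 1.2 = 180 per arm.

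**Assumptions.** Centres are the randomised units, split 6 v 6, with 150/6 = 25 completers each. SD 1.5 is not already reduced for baseline. The ICC values are illustrative.

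**1. The plan's own figure.** n per arm = 2 × (1.960 + 0.842)² × 1.5² / 0.5² = 141.3, so 142 (143 with a t-test). The stated 150 is consistent with rounding up. At 150 per arm the standard error is 1.5 × √(2/150) = 0.1732, and 0.5/0.1732 = 2.887. Power is 82.3% with normal limits and 82.1% with t on 298 df. This is the calculation for individual randomisation.

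**2. The same inputs with 12 centres, ICC 0.** The non-centrality stays at 2.887 and the critical value becomes t(0.975, 10 df) = 2.228. Power from the non-central t is **74.0%**. Other cases at ICC 0:
- 144 per arm (180 × 0.8, the number left after the stated dropout): 72.2%.
- 8 df, if two stratum terms are fitted (assumed): 71.6%.
- Completers needed for 80% on 10 df: about 175 per arm.

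**3. Positive ICC.** Design effect = 1 + 24 × ICC; the non-centrality is 2.887/√(design effect).

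| ICC (assumed) | Design effect | Power, normal limits | Power, t on 10 df |
|---|---|---|---|
| 0 | 1.00 | 82% | 74% |
| 0.005 | 1.12 | 78% | 69% |
| 0.01 | 1.24 | 74% | 65% |
| 0.02 | 1.48 | 66% | 57% |
| 0.05 | 2.20 | 49% | 42% |

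At ICCs of 0.01 and 0.02 a design effect with normal limits still overstates power by about 9 points.

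**4. Baseline adjustment.** If SD 1.5 is unadjusted and baseline HbA1c correlates ρ with follow-up (assumed, the same reduction applied between and within centres), the variance is multiplied by 1 − ρ². At ICC 0 on 10 df, power is 78%, 81% and 85% for ρ = 0.3, 0.4 and 0.5. At ICC 0.02 with ρ = 0.5, the non-centrality is 2.887/√(0.75 × 1.48) = 2.740 and power is 70%.

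**5. Type I error.** Simulation of 12 centres of 25, 200,000 trials per ICC, random-intercept model with centre always included, variance estimates truncated at zero:

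| ICC | REML, ±1.96 | ML, ±1.96 | t-test on centre means, 10 df |
|---|---|---|---|
| 0 | 3.9% | 4.5% | 4.9% |
| 0.01 | 5.3% | 6.3% | 5.0% |
| 0.02 | 6.3% | 7.7% | 5.0% |
| 0.05 | 7.3% | 9.5% | 5.0% |

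**The case against.** **The analysis text contains no stated error.** A reader might infer that the trial will test against 1.96 and so exceed 5%. The document does not support this. It names no reference distribution, the sample size fits a t-test as well as normal limits, and a degrees-of-freedom method is often left to the statistical analysis plan. Nor is the excess error unconditional: it is absent at ICC 0, small for REML at ICC 0.01, and the document gives no ICC. This objection stands, so the small-sample test is offered as an improvement that closes a risk.

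**The 74% is not the power of the planned analysis.** The Data analysis section specifies regression on 12-month values with baseline as a covariate, which could lift power above 80% at ICC 0. This also stands, so 74% must be given as a conditional figure. It does not rescue the stated 80%: even ρ = 0.5 gives 70% at ICC 0.02, and the calculation mentions no baseline correlation.

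**The size of the loss depends on the comparison.** At 150 per arm the fall is from 82% (individual-level test) to 74%. Against a multilevel test at 1.96, which has about 78% power at ICC 0, the change of reference distribution costs about 4 points.

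**The randomised unit is not stated consistently.** The Abstract has patients being randomised by community staff, Study design refers to geographical location, Group allocation to centres, and the Sample size calculation to groups of 8 to 15. If those groups were the independent units, there would be about 300/15 = 20 to 300/8 ≈ 38 clusters and more degrees of freedom. But the Intervention section forms such groups only in the intervention arm, under peer leaders, and describes none for controls. Centres remain the best reading.

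**Conclusion.** The point holds for the sample size. The stated 80% power comes from an individual-level calculation and does not follow for a trial that randomises 12 centres. On the plan's own difference, SD and completers, a centre-level test without baseline adjustment has 74% power at ICC 0 (72% with 144 per arm), and about 65%, 57% and 42% at ICCs of 0.01, 0.02 and 0.05. These figures rest on a 6 v 6 split, 25 completers per centre, SD 1.5 unadjusted, and centres being the randomised units.

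For the analysis the conclusion is weaker. Large-sample limits would be too liberal if between-centre variation is real (REML about 6% at ICC 0.02 and 7% at 0.05), and the plan leaves open whether it will use them. It should be amended, at little cost.

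**What to change.** - **Sample size calculation:** restate power for 150 (and 144) completers per arm using about 10 df (12 centres minus 2, fewer if strata are fitted), over a stated range of ICCs. Say whether SD 1.5 is before or after baseline adjustment, and give any baseline correlation relied on.
- **Data analysis:** state that the arm effect is tested with centre as a random effect, by REML with Kenward-Roger or Satterthwaite degrees of freedom, or by a t-test on baseline-adjusted centre means.
- **Unit of randomisation:** reconcile the Abstract, Study design and setting, Group allocation and Sample size calculation, since the degrees of freedom depend on it.

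**Cost:** a few sentences and no additional enrolment. The stated power will be less favourable. The interval will be up to 2.228/1.96 = 1.14 times as wide for the same standard error. A REML model held to 10 df is conservative when the ICC is near zero (simulated type I error 1.9% at ICC 0 and 2.9% at 0.01); the t-test on centre means stays at about 5%.
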